## Abstract

**Background:**

Acute pancreatitis is a serious threat to human health and gastrointestinal dysmotility is a common complication for acute pancreatitis patients, resulting in delayed feeding, oral feeding intolerance, paralytic ileus, and abdominal compartment syndrome. Currently, there are limited treatment for this complication.

Neostigmine is known to increase gastrointestinal motility and has been used to treat gastrointestinal dysmotility after surgery. However, research in treating acute pancreatitis with neostigmine is currently limited.

**Methods:**

This trial is a randomized, placebo-controlled, double-blinded, mono-centric trial that will test the hypothesis that neostigmine can improve gastrointestinal motility in patients with severe acute pancreatitis. Up to 56 patients will be randomized in this study receiving 0.5 mg/1 ml of neostigmine methylsulfate injection twice per day or 1 ml of saline injection twice per day. Defection time (aim 1), mortality and organ failure (aim 2), borborygmus, starting of enteral nutrition and intra-abdominal pressure (aim 3), and length of ICU and hospital stay (aim 4) will be assessed.

**Discussion:**

Findings from this study will provide data supporting the usage of neostigmine for treating severe acute pancreatitis patients with gastrointestinal dysmotility.

**Trial registration:**

This study is registered on chictr.org.cn with the identifier as ChiCTR2200058305. Registered on April 5, 2022.

## Administrative information

Note: the numbers in curly brackets in this protocol refer to SPIRIT checklist item numbers. The order of the items has been modified to group similar items (see http://www.equator-network.org/reporting-guidelines/spirit-2013-statement-defining-standard-protocol-items-for-clinical-trials/).

## Introduction

### Background and rationale {6a}

Acute pancreatitis (AP) is a seriousthreat to human health globally. It is the third most common gastrointestinal, liver, and pancreatic principal diagnoses from hospital admissions in USA. Over 275,000 patients were admitted because of AP every year, with over 2000 deaths and 2,600,000,000 dollars spent [1–3]. The diagnosis of AP requires 2 of the following features: characteristic abdominal pain, biochemical evidence of pancreatitis, radiographic evidence of pancreatitis. AP can be categorized as mild, moderately severe, or severe based on the revised Atlanta classification [4]. Severe acute pancreatitis (SAP), defined as pancreatitis with persist organ failure (over 48 h), develops in 20–30% of AP patients, with high mortality (15%) [5, 6].

Gastrointestinal dysmotility is a common complication for AP patients, often resulting in abdominal distension, nausea, and vomiting. Delayed feeding and oral feeding intolerance (OFI) may also be associated with gastrointestinal dysmotility. Severe gastrointestinal dysmotility is associated with paralytic ileus and abdominal compartment syndrome (ACS), which can be lethal for SAP patients [7–9]. Currently, there is limited evidence for treating gastrointestinal dysmotility in AP patients.

Early enteral nutrition (EN) plays an important role in the management of AP by protecting the mucosal barrier and reducing bacterial translocation. Delayed feeding (generally defined as over 24 h after onset) is associated with higher rates of infected peripancreatic necrosis, multiple organ failure, and total necrotizing pancreatitis [10–14]. OFI is a well-known complication of AP and the burden can be high. OFI develops in nearly one in six patients with AP, leading to longer length of hospitalization and reduced quality of life [15–19]. ACS, defined by the increased intra-abdominal pressure > 20 mmHg in association with failure of at least one organ system, developed in 12% to 56% of patients and the mortality of SAP patients with ACS is around 24 to 75% [20–24].

Neostigmine, an acetylcholinesterase inhibitor (ACI), is known to increase upper and lower gastrointestinal motility [25–27]. It has been used for postoperative recovery of gastrointestinal function [28, 29]. One study have shown that neostigmine could reduce intra-abdominal pressure (IAP) in SAP patients [30]. however, this is a single-center study with small sample size and no blinding was used. Further evidence is needed and this study aims to evaluate the efficacy and safety of neostigmine on treating patients with SAP.

The first defection time is a defined as the time span from the onset of disease to the first defection. Spontaneous defection is usually an indicator for starting EN in clinical practice and is widely used in researches on gastrointestinal obstruction [31–33]. One [34] research investigating transcutaneous electrical acustimulation for treating acute pancreatitis used first defection time as an important endpoint. In this study, we choose the first defection time as our primary outcome.

### Objectives {7}

The objective of this study is to investigate the efficacy and safety of neostigmine on treating SAP and to evaluate whether it can promote the recovery of intestinal function, making spontaneous defection and EN usage earlier, decrease intra-abdominal pressure, reduce mortality, organ failure and shorten hospital stay.

### Trial design {8}

This study is a randomized, placebo-controlled, double-blinded, mono-centric, superiority trial. All eligible participants will be randomly divided into intervention group or control group in a 1:1 ratio. Participants will be followed up until they are discharged. The flow chart of this study is shown in Fig. 1.

**Fig. 1 Fig1:**
[figure not shown]
Flow chart of the study

## Methods: participants, interventions, and outcomes

### Study setting {9}

The study will be conducted in the emergency department and intensive care unit (ICU) department of Peking Union Medical College Hospital (PUMCH), a grade III level A hospital in China.

### Eligibility criteria {10}

The detailed inclusion and exclusion criteria are outlined in Table 1. Briefly, patients with newly onset of acute alcoholic or hyperlipidemia AP and evidence of organ failure will be included. Patients that have contraindication to neostigmine methylsulfate injection or other severe diseases will be excluded.

**Table 1 Tab1:** Eligibility criteria

Inclusion criteria	Exclusion criteria
• Aging between 18 and 75 • Diagnosed with alcoholic or hyperlipidemia acute pancreatitis • Evidence of organ failure (according to Marshall scoring system)	• Allergic to neostigmine methylsulfate injection • Contradiction to neostigmine methylsulfate injection ▪ Epilepsy ▪ Angina, arrhythmia, ventricular tachycardia, sinus bradycardia, ▪ Mechanical intestinal obstruction, urethra tract obstruction, asthma ▪ Uncontrolled hypotension, elevated vagus nerve tone • Pregnancy • Uncontrolled hypertension and severe cardiocerebrovascular disease

### Who will take informed consent? {26a}

Informed consent will be obtained by a member of study team.

For any AP patients who visit the emergency department of PUMCH and meets the inclusion and exclusion criteria, they will be approached to participate in the study by one of the investigators from the study team. The investigator will be responsible for providing each patient with an informed consent form (ICF) about the study’s purpose and procedures, foreseeable benefits and potential risks of participation, compensation for any potential harms, data protection procedures, and option to withdraw from the study at any time and without any given reason, which should be read by the patient. The investigator will answer any questions the patient may have, and both the patient and investigator will sign the ICF to indicate the patient’s full understanding of the protocol. Written informed consent must be obtained for all participants prior to any intervention.

### Additional consent provisions for collection and use of participant data and biological specimens {26b}

This trial does not involve collecting biological specimens. In the informed consent form, participants will be asked if they agree to use their data for further analysis and sharing with researchers relevant to this study should they choose to withdraw from the trial.

### Interventions

#### Explanation for the choice of comparators {6b}

The dose of neostigmine used in this trial (0.5 mg twice a day) has been chosen based on the guidance from FDA [35]. One milliliter of saline will be used as placebo, which will be taken identically.

#### Intervention description {11a}

Participants will be randomized in a 1:1 ratio via computer-generated sequence randomization. The study will be blinded to participants. Neostigmine methylsulfate injection and the saline are prepared by pharmacists who are not involved in the study and are identical visually.

For experiment group, 0.5 mg/1 ml of neostigmine methylsulfate injection will be injected intramuscularly at the deltoideus triangularis twice a day right after the enrollment. For control group, 1 ml of 0.9% NS will be injected intramuscularly at the deltoideus triangularis twice a day.

Apart from intervention, other treatment of AP will be performed according to American Gastroenterological Association Institute Guideline [36].

#### Criteria for discontinuing or modifying allocated interventions {11b}

Adverse events determined by clinical doctors will be reported to the study team and IRB. The study team will determine whether the event is likely to be due to intervention and whether to discontinue the study medication. The IRB will review the event routinely and determine whether it is safe to continue the study.

#### Strategies to improve adherence to interventions {11c}

All participants will be informed of the study procedures, as well as potential benefits and risks to make them fully understand the significance of their involvement in the study. The study team will check the nursing document of each participant routinely to determine that the participants are taking intervention properly.

#### Relevant concomitant care permitted or prohibited during the trial {11d}

There will be no restrictions regarding concomitant care during the trial.

#### Provisions for post-trial care {30}

Not applicable. Study participants will exit the study after discharging from hospital. There will be no further follow-up.

### Outcomes {12}

#### Primary outcome

The effect of neostigmine on gastrointestinal motility will be assessed using time span from onset of disease to the first time of spontaneous defection (defined as at least 1 h apart from enema). The defection times will be documented by clinical doctors and reported to study team for documentation.

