#### Sample size {14}

This is a randomized controlled trial. The bilateral significance level is 5% with an assurance of 90%. We estimate the standard deviation is 36 h, and the mean difference is 36 h. In the case of 1:1 ratio between intervention group and control group, a total of 44 patients will be needed (22 patients in each group). Considering a 20% drop-out rate, 56 patients will be recruited.

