## Discussion

Gastrointestinal dysmotility is a common complication in AP patients, which can lead to delayed feeding and OFI. There is little evidence regarding the treatment of gastrointestinal dysmotility induced by AP. Neostigmine can increase gastrointestinal motility and has been used to treat gastrointestinal dysmotility after surgery. With this randomized, placebo-controlled trial, our aim is to investigate whether neostigmine is safe and efficacy for treating AP patients with gastrointestinal dysmotility. We would like to discuss some aspects and challenges of the study design in detail below.

First, the enrollment of patients: a diagnosis of SAP requires persist organ failure, which is defined as organ failure lasting over 48 h [4]. However, early intervention [38] plays an important role in treating AP patients, so we start intervention on patients within 24 h of onset, which will lead to brief intervention on moderate-severe acute pancreatitis patients.

Another point we would to address is the COVID-19 pandemic, which may lead to fewer patients, disturbing patient enrollment and even temporary interruption of the research. A delayed end of this study may occur.

In conclusion, a positive outcome of this trial will provide strong evidence as to the safety and efficacy of neostigmine in treating the gastrointestinal dysmotility for AP patients.

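### The primary outcome is timed from disease onset and can be fixed by a stool passed before the first injection, which dilutes the effect and costs power but does not bias the comparison

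*Protocol article*

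**What the plan says.** - **Outcome.** The Primary outcome section measures the "time span from onset of disease to the first time of spontaneous defection". The only condition on a countable stool concerns enemas: "defined as at least 1 h apart from enema". Background and rationale {6a} uses the same origin, "the time span from the onset of disease to the first defection", there without the word spontaneous.
- **Eligibility.** The text above Table 1 says that "patients with newly onset of acute alcoholic or hyperlipidemia AP and evidence of organ failure will be included" and that "Patients that have contraindication to neostigmine methylsulfate injection or other severe diseases will be excluded". Table 1 lists age, aetiology and organ failure, then the exclusions. It does not mention earlier defecation or time since onset.
- **Start of treatment.** The Discussion states "we start intervention on patients within 24 h of onset". Table 1 does not carry this limit.
- **Other time outcome.** Timing of enteral nutrition, under Secondary outcome, is counted from randomisation.
- **Analysis.** Section {20a} plans Student's t-test and an intention-to-treat set that keeps everyone randomised. Sections {16a} and {20b} plan no stratification and no adjusted analysis.
- **Sample size {14}.** Two-sided 5%, 90% power, SD 36 h, difference 36 h, 22 per arm, 56 recruited after a 20% drop-out allowance. The section does not say whether the two 36 h figures are counted from onset or from randomisation.

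**The concern.** The outcome should be something the drug still has a chance to change when the patient is randomised. With the clock starting at onset, two things that precede treatment enter the outcome.

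The first is the interval from onset to randomisation, which is added to every patient's value. The second is any spontaneous stool passed in that interval. Read literally, such a stool ends the clock before the first injection, and nothing in the definition or in Table 1 prevents it. The patient then contributes no treatment effect but still counts in the denominator.

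What is at stake is the trial's ability to detect the effect it was planned for. This is the only outcome with a sample-size calculation. If a material share of patients had outcomes settled before dosing, a null result could not separate an ineffective drug from a diluted comparison.

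**Working it through.** **Inputs.** From Sample size {14}: difference 36 h, SD 36 h, two-sided 5%, 90% power, 22 per arm, 20% drop-out. From the Discussion: treatment within 24 h of onset. Assumed, because the documents give neither: the share f of patients with a qualifying stool before the first dose, and a uniform spread of onset-to-randomisation time.

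**1. The plan's own figure.**
n per arm = 2 × (1.960 + 1.282)² × 36² / 36² = 21.01, rounded up to 22, so 44 in total. Drop-out: 22 / 0.8 = 27.5, rounded up to 28, so 56 in total. The stated figures reproduce. With the noncentral t distribution (42 degrees of freedom), 22 per arm gives 89.97% power.

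**2. Stools before treatment.**
If a share f of each arm cannot respond and the rest have the planned effect, the expected difference is 36 × (1 − f). With the SD held at 36 h, the noncentrality is that difference divided by 36 × √(2/22) = 10.85 h.

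| f (assumed) | Difference (h) | Noncentrality | Power, 22 per arm | Power, 28 per arm | Evaluable / recruited for 90% |
|---|---|---|---|---|---|
| 0% | 36.0 | 3.32 | 90% | 96% | 44 / 56 |
| 10% | 32.4 | 2.99 | 83% | 91% | 52 / 66 |
| 20% | 28.8 | 2.65 | 74% | 84% | 66 / 84 |
| 30% | 25.2 | 2.32 | 62% | 73% | 86 / 108 |

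Powers use the noncentral t. The last column uses the normal approximation, as in step 1. The 28-per-arm column is the best case, in which none of the 56 patients is lost. Holding the SD at 36 h is a simplification: a mixture of early and late stools could raise or lower it.

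**3. Time before treatment.**
A uniform delay over 0 to 24 h has SD 24 / √12 = 6.93 h.
- If the planned 36 h SD is counted from randomisation, the onset-based SD is √(36² + 6.93²) = 36.7 h and power is 88.9%, a loss of about one point.
- If the 36 h SD is already counted from onset, it contains this variation and there is no loss against the plan. The SD from randomisation would then be √(36² − 6.93²) = 35.3 h, so moving the clock would take power from 90% to about 91%.
- The chance difference between arms in mean delay has a standard error of 6.93 × √(2/22) = 2.1 h, against a planned difference of 36 h.

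**The case against.** The strongest reply is that randomisation deals with the problem. Delay and earlier stools have the same expected distribution in both arms, the common lead time cancels in the difference in means, and the type I error rate is unaffected. This stands. A reader might infer that pre-treatment events are credited to the drug, or that a chance imbalance in delay would pass for an effect. The documents do not support that: any imbalance is ordinary sampling error covered by the 5% level, and dilution works against the drug.

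A reader might also take the silence of Table 1 to mean that delays of several days are possible, with a much larger SD. That does not fit the text. The Discussion states 24 h, and Recruitment {15}, though hard to read, places randomisation and first treatment before the organ-failure check at 48 h after onset. The missing limit is an inconsistency to reconcile, not evidence that there is no limit.

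The shares of 10% to 30% are assumptions. In patients with organ failure who are treated within a day of onset, the true share could be near zero, and then little power is lost. If the 36 h difference came from a population timed from onset that included early stools, some dilution is already in it. Both points stand and limit what can be said about size.

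Finally, timing from onset is a declared choice, for which the Background points to use of first defecation time in an earlier acute pancreatitis study. A different origin for enteral nutrition is not a contradiction, since it is a different outcome. Nor is the lack of a dysmotility criterion an error in itself, because the Objectives concern severe acute pancreatitis. None of this answers the central point: the definition allows an outcome that is complete before treatment starts.

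**Conclusion.** The point holds as a weakness of efficiency and clarity in the primary outcome, not as a source of bias towards the drug. Followed as written, the plan lets a stool before treatment settle a patient's primary outcome and keeps that patient in the intention-to-treat comparison.

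The size depends on a frequency that the documents do not give. Each 10% of patients affected removes 3.6 h from the expected difference; over the assumed range of 10% to 30%, power falls to between 83% and 62% at the planned 22 per arm. This assumes that the 36 h effect applies to patients without an earlier stool and that the SD stays at 36 h. The lead-time component is minor within the 24 h window. The sample-size arithmetic itself is sound; what it lacks is a stated time origin.

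**What to change.** 1. Define the primary outcome as time from randomisation to the first spontaneous defecation after randomisation, keeping the enema rule. Use the same definition in the Background.
2. State in Sample size {14} that the 36 h difference and 36 h SD refer to that interval, or revise them if they do not.
3. Reconcile Table 1 with the 24 h statement in the Discussion.
4. Record whether a spontaneous stool occurred between onset and randomisation, and report this by arm.

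Optional: an entry criterion of no spontaneous stool since onset, and onset-to-randomisation time as a pre-specified covariate. The lead-time figures above do not make the covariate necessary. The entry criterion might slow recruitment.

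The cost is mainly wording plus one extra data item; randomisation time is already needed for the enteral nutrition outcome. Results would be less directly comparable with studies that time defecation from onset, so the onset-based time can be kept as a secondary outcome. Moving the clock does not guarantee the full 36 h effect in patients whose bowels had already moved, which is why item 4 matters.

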#### Secondary outcome

Mortality of patientsNew-onset organ failure, defined as organ failure after randomization (not present at any time before randomization). Including respiratory failure (PaO_2_/FiO_2_ ≦ 300, or requirement of mechanical ventilation), circulatory failure (systolic blood pressure < 90 mmHg, despite adequate fluid resuscitation, or requirement for inotropic catecholamine support) and renal failure (creatinine level > 177 μmol/L after rehydration or new need for hemofiltration or hemodialysisIntra-abdominal pressure, measured indirect using bladder pressure [37] every day after enrollmentTiming of EN, defined as time from randomization to the initiation of tolerated ENBorborygmus, measured every day by member of study teamOccurrence of abdominal infection, based on the diagnosis when dischargingThe proportion of adverse events and serious adverse events identified in both groupsHealth economics, including length of ICU stay, length of hospital study, and total cost in hospital, documented based on hospital information system

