#### Recruitment {15}

A total of 56 patients will be recruited and participate in the study. Prior to recruitment, investigators will carefully study the medical history, laboratory test, and imaging test of each patient. If the patient meets the inclusion and exclusion criteria, researchers will fully consider the compliance of the patients and informed consent forms (ICFs) will be obtained before collecting any data or performing any intervention. After initial assessment and randomization, patients will receive intervention and 48 h after onset. If the patient still has evidence of organ failure, they will be diagnosed with SAP and will be formally enrolled in the study. The follow-up will be ended when the patients leave the hospital.

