### Data collection and management

#### Plans for assessment and collection of outcomes {18a}

Sociodemographic characteristics and required clinical information will be obtained from the hospital information system of PUMCH. IAP and borborygmus of participants will be measured every day by the researcher. A third person with adequate clinical acumen independent to the project will assess the data collected. If inappropriate data is discovered, study team will be notified to remedy the error.

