### Statistical methods

#### Statistical methods for primary and secondary outcomes {20a}

Intention-to-treat (ITT): Nno one was excluded from the main analysis set after randomizationPer-protocol set (PPS): good compliance case data that meets the main inclusion and exclusion criteria and reach the primary endpoint

The number of participants selected and complete the study will be listed and the two analysis data sets (ITT and PPS) as specified above will be identified. Cases of protocol violation will also be listed with reasons documented. In terms of outcome indicator analysis, continuous variable indicators will count the number of cases (*n*), mean (*x*), standard deviation (SMD), median (*M*), minimum (min), and maximum (max). The difference between groups will be analyzed using Student’s *t*-test. Counting and grading data will be used to calculate the frequency and composition ratio. The *χ*
^2^ test/chi-square test will be used for differences between groups. Unless otherwise stated, all statistical tests will be conducted in a bilateral manner. All data will be entered in Microsoft Excel, and all statistical analyses will be performed using the SPSS version 25 statistical package.

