#### Methods for additional analyses {20b}

Currently, there is no planned additional subgroup or adjusted analyses.

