#### Methods in analysis to handle protocol non-adherence and any statistical methods to handle missing data {20c}

An ITT data set will be used for protocol non-adherence and no imputation of missing data will be performed for statistical analysis.

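### Daily intra-abdominal pressure has no single pre-stated comparison: the plan gives only an unadjusted two-group t-test, which needs one value per patient

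*Protocol article*

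**What the plan says.** Under Secondary outcome, IAP is "measured indirect using bladder pressure" on each day after enrolment. Plans for assessment and collection of outcomes {18a} repeats the schedule: "IAP and borborygmus of participants will be measured every day by the researcher". Recruitment {15} says "The follow-up will be ended when the patients leave the hospital", so the length of the series differs between patients.

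For continuous variables, Statistical methods {20a} lists descriptive statistics and then one comparison: "The difference between groups will be analyzed using Student’s *t*-test". It makes no exception for outcomes measured repeatedly. Methods for additional analyses {20b} adds: "Currently, there is no planned additional subgroup or adjusted analyses". Section {20c} says "no imputation of missing data will be performed for statistical analysis". Who will be blinded {17a} leaves the data analysts unblinded.

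The readable text names no analysis day, window, summary measure or repeated-measures model for IAP. The participant timeline (Table 2) is not shown.

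**The concern.** The outcome yields many values per patient and the stated test accepts one. The gap can be filled in at least three ways: test every day, choose one day, or collapse the series into a mean, peak or change. These can give different answers, and the choice falls to analysts who can see the allocation.

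Two further points follow.

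- No stated analysis adjusts for starting pressure. Randomisation is unstratified in 44 to 56 patients, so chance imbalance in starting pressure is possible and precision is scarce.
- The series ends at discharge or death and nothing is imputed. Any comparison on a later day would include only patients still in hospital. Shorter stay and lower mortality are themselves objectives of the trial, so that subset may differ between arms because of treatment.

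Lowering IAP is a named objective, and the Background cites an earlier small, unblinded study of IAP as part of the rationale. A clear IAP result is therefore worth having, although IAP is one of several unranked secondary outcomes.

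**Working it through.** **The plan's own figure.** Sample size {14} gives SD 36 h, difference 36 h, two-sided 5% and 90% power. Per arm, n = 2(1.960 + 1.282)² × (36/36)² = 21.0, rounded up to 22. The t-based solution is 22.02, with power 0.900 at 22. With 20% drop-out, 22/0.8 = 27.5, so 28 per arm and 56 in total. The stated 44 and 56 reproduce. They concern the primary outcome; the protocol gives no figures for IAP.

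**Assumptions for IAP.** There are 22 per arm, complete series of 5, 7 or 10 days, equal variance each day, and the same correlation ρ between any two readings of a patient, with ρ from 0.4 to 0.8. None of these except the 22 comes from the protocol.

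**If each day were tested at 5% with no true effect.** With independent days the chance of at least one p < 0.05 is 1 − 0.95^k: 22.6%, 30.2% and 40.1% for k = 5, 7 and 10. With correlated days, simulation (100,000 trials per cell) gives:

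| Days | ρ = 0.4 | ρ = 0.6 | ρ = 0.8 |
|---|---|---|---|
| 5 | 19.8% | 16.8% | 12.8% |
| 7 | 25.1% | 20.7% | 15.2% |
| 10 | 32.5% | 25.4% | 17.5% |

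**If each day were tested and a constant effect of 0.6 SD existed (assumed).** With ρ between 0.5 and 0.7, some days would be significant and others not in 52–67% of trials over 5 days and in 60–76% over 7 (10,000 simulated trials per setting).

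**Value of the starting pressure for one window-mean contrast.** Take the single-day variance as 1.

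- Variance of the k-day mean: V = [1 + (k − 1)ρ]/k.
- Its covariance with a pre-injection reading is ρ, so the adjusted variance is V − ρ² and the proportional reduction is ρ²/V.
- k = 5, ρ = 0.4: V = 2.6/5 = 0.52; reduction 0.16/0.52 = 31%.
- k = 10, ρ = 0.8: V = 8.2/10 = 0.82; reduction 0.64/0.82 = 78%.
- A change score has variance V + 1 − 2ρ, which exceeds the adjusted variance by (1 − ρ)². Adjustment is therefore never worse. At k = 5, ρ = 0.4 the change score (0.72) is even worse than ignoring baseline (0.52).

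These variances ignore the one degree of freedom spent on the covariate. If correlation with baseline fades over the days, the gain is smaller.

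**The case against.** A reader might infer that the protocol plans a test on every day. It does not say so. The t-test sentence is generic and applies equally well to one mean, peak or change score per patient, which would be a single valid test. The false-positive figures are therefore conditional and are not properties of the stated plan.

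A reader might also infer that baseline pressure is thrown away. That goes too far. A change score would use it, and section {20b} says only that no adjusted analyses are currently planned, which is weaker than excluding them. With Table 2 not shown, it cannot be known whether a pre-injection reading is scheduled.

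It can also be said that the window, summary and model for a secondary outcome are ordinary analysis-plan content. That has force against a complaint of mere omission. It does not fully answer the point, because the protocol does fix something: one t-test for continuous outcomes, with no adjusted analysis planned. What it fixes does not fit a daily outcome without a further choice, and it passes over a more precise method that is cheap to adopt.

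Finally, a mixed model assumes that missing readings are missing at random and does not resolve truncation by death or by discharge on recovery. This stands, and the fix has to address it separately.

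**Conclusion.** The point holds in a limited form. The stated test does not match an outcome measured daily until discharge, no single IAP comparison is fixed, the choice is open to unblinded analysts, and no stated analysis adjusts for starting pressure.

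Its size is conditional. Only if daily tests were run would the chance of a false positive somewhere reach about 13–20% (5 days), 15–25% (7) or 17–33% (10). A baseline-adjusted window mean would have about 31–78% less variance than an unadjusted one. Both ranges rest on an assumed constant correlation of 0.4 to 0.8 and complete series.

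IAP is secondary and carries no confirmatory claim, so this is a desirable improvement to the interpretability and precision of one outcome. It does not touch the primary outcome or the sample size.

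**What to change.** In sections {20a} and {20b}, pre-state one IAP contrast over a short fixed window counted from randomisation, for example the between-arm mean difference averaged over the window. Estimate it with a mixed model for the daily values, or with an ANCOVA of each patient's window mean, adjusting for the bladder pressure taken before the first injection. Present by-day values as description only.

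Confirm that the first reading precedes the first injection. The text is unclear here: IAP is measured after enrolment, the intervention description starts injections right after enrolment, and Recruitment {15} places formal enrolment 48 h after onset, once treatment has begun. These passages need to be reconciled so that day 1 of the series is defined.

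State how patients who die or are discharged within the window enter the contrast, and report their numbers by arm.

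The cost is a few sentences of analysis wording, a little more analysis work (SPSS 25 fits either model) and possibly an earlier first reading. No extra patients are needed.
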